## Assessment and management of risk

There are minimal risks associated with taking part in the PERSONAL-AGILITY study. Participants will be made fully aware of any potential risks before consenting. All research investigations are detailed in the participant information sheets and will be explained to the participant before each investigation to ensure that they are willing to undertake each one.

### Outcome testing

For frailer participants with lower functional ability, and who may be at increased risk of falls, objective tests of physical function such as the SPPB may make some people feel uncomfortable or unsteady, because it asks them to perform at a level that they may be unaccustomed to. Considering this, function tests will be performed in the presence of another person (staff, relative or carer where possible) and participants may defer the test if they do not feel safe. The participant will be able to cease testing whenever they wish.

For the measurement of movement behaviours, although the accelerometer is a lightweight and non-invasive device some participants may find these uncomfortable to wear over 9 days. Should this be the case, participants will be able to remove the device whenever they wish.

Finally, the PROMS may bring to light conditions and concerns requiring onward referral and ongoing support. PROMs used in both the trial and as part of the intervention will be reviewed immediately after collection and values raising concern will be discussed with the participant and, where necessary, flagged with their GP. Indicators of concern may include (but are not limited to):

- High levels of anxiety and depression
- New or worsening symptoms, including changes in health or new injury or trauma
- High levels of emotional distress
- High levels of carer burden

Testing conducted in participants homes may be subject to increased risk for the researcher. These risks will be minimised by adhering to the UHL lone working policy.

### Intervention

The study population will include people with MLTCs and frailty and consequently these participants may be at increased risk of falls or have a previous history of falls. Intervention providers and health and care practitioners will be made aware of falls risk and history and advice and interventions will be tailored to minimise the risk of future falls as far as possible.

The PERSONAL-AGILITY intervention will use digital technology in synergy with face-to-face contact to compliment and provide flexibility whilst maintaining the personal touch of direct face-to-face interaction between the service user and the HCPs. Whilst digital platforms are neither geographically-nor time-restrained and therefore may be particularly appealing for adults with MLTCs conditions and frailty and their carers, given their circumstances and priorities, there are potential risks associated. Steps for health includes a discussion forum, which could leave users open to adverse behaviours such as bullying, and provision of misinformation between users. To minimise any potential risks, we will utilise approaches from our previous programmes and extensive expertise in developing and monitoring online support groups. These include:

- Outlining an ‘acceptable use policy’ at registration
- Using an experienced moderator (someone who oversees the discussion forum on Steps for health and reviews content to ensure every post meets the site's standards, restricting any offensive behaviour, content, or writing. The whole platform including the chat forum is regularly checked/ monitored by designated LDC staff

As the PERSONAL-AGILITY study will use digital technology some participants may be at risk of digital exclusion. To limit the risk, technology will be explained in face-to-face appointments, and individualised support provided as required. Furthermore, participants will be given details (phone and email) of who to contact for IT support. Simple user guides will also be created to support use, in line with PPI feedback.

Where the intervention involves support from a physical activity officer, we will request that participants are only referred into safe and appropriate groups for their level of health and physical ability.

There may be some risks associated with becoming more active and sitting less. These include a slightly elevated risk of falls for people who have had a previous fall. Overall, previous research tells us that the benefits of being more physically active far outweigh the risks of active, and that in the long run sitting more does not make people at risk of falls safer. We will ensure that participants are well enough to take part in the programme as part of the screening process, and we will also make sure that they receive a programme which takes into account any previous falls you may have had to ensure that it is right for your needs. Some physical activities can be associated with short-term muscle aches which are normal, but can be uncomfortable, particularly if participants are not used to being physically active.

There are minimal risks associated with the interventions we will use to support participants to improve their sleep, but for some people with severe insomnia they may not be effective and could lead to frustration, or possibly worsening sleep habits. We will track this closely throughout the intervention, and refer these participants back to their GP if we suspect that they may need more in-depth support, or that they might have an underlying condition which requires treatment.

### Participation burden

Whilst the PERSONAL-AGILITY intervention aims to minimise the burden of treatment, using a person-centred, shared decision-making, approach, we acknowledge that any burdens associated with the intervention may only come to light during or after their involvement. To understand this, participants will be asked to participate in an interview as part of the mixed methods process evaluation. The focus of these interviews will be to explore the dynamic of user experience and implications for burden. We will also use a questionnaire to measure the 24-hour physical behaviours burden to further explore the burden of treatment associated with the PERSONAL-AGILITY intervention. This will allow further exploration of the burden of treatment within long term conditions, frailty and carer burden and complement the understanding gathered through our qualitative work.

Individuals with multiple long term conditions and frailty as well as their carers, often have complex lives, marked by a wide range of appointments and tasks associated with managing their conditions, or the conditions of those they care for ^114^. The time commitment needed to take part in this study may represent a burden to participants. The burden may be greatest to those within the intervention group, as this group will be asked to complete both the PERSONAL-AGILITY intervention and the assessment visits. This has been discussed extensively with the study PPI/E group, and consequently we will use a range of strategies to both understand and reduce the potential burden to participants. These include:

- Offering participants, the ability to opt out of the interviews
- Arranging study visits and interviews at the participant’s convenience, using a range of options (in person, telephone or online) to support participation and avoid the need for an additional visit to the hospital. Locations for in-person visits may also include the home and community locations where possible
- Organising the secondary PROM outcome in order of priority to the research team, and offering participants support to complete the PROMs
- Selecting only intervention measures which are relevant and important to the participant.

### Mixed methods process evaluation

Interviews will be in-depth and will follow a topic guide but also be semi-structured to allow for the exploration of other areas that are important to or significant for the participant, in relation to the research questions. Interviews may include discussion of health issues which significantly impact upon participants health and may mean that participants discuss emotive and distressing topics, or issues which they feel strongly about. The researcher will remain sensitive to the signs of distress and discomfort during the interviews and ask the participant if they wish to continue or would prefer to end the interview or move on to a new topic. In the case of significant distress, the participant will be referred to their care provider for further support.

The small number of participants involved in the qualitative study may lead to concerns about individual identification. Responses will be confidential, and data anonymised and this will be made clear to participants in the PIS, during the consent procedures and reiterated prior to the interview commencing. Finally, to enable assessment of fidelity, PERSONAL-AGILITY study sessions or assessments will be audio recorded. All participants will be asked for their consent to be recorded.

## End of trial

End of study will be defined as 12 months following the collection of outcome data at the 24 weeks visit of the last participant to allow sufficient time for sample analysis. The sponsor must notify the REC of the end of a clinical trial within 90 days of its completion.

# Recording and reporting of serious adverse events (SAEs)

## Definitions

Table 4.Definitions for SAEs

| **Term** | **Definition** |
| --- | --- |
| Adverse Event (AE) | Any untoward medical occurrence in a participant or clinical investigation, which does not necessarily have to have a causal relationship with this treatment.  An AE can therefore be any unfavourable and unintended sign (including an abnormal laboratory finding), symptom or disease temporally associated with the study, whether or not considered related to the study. |
| Serious Adverse Event (SAE) | A serious adverse event is any untoward medical occurrence that:   - Results in death - Is life-threatening* - Requires inpatient hospitalisation or prolongation of existing hospitalisation - Results in persistent or significant disability/incapacity - Consists of a congenital anomaly or birth defect - Other important medical events**   *The term "life-threatening" in the definition of "serious" refers to an event in which the participant was at risk of death at the time of the event; it does not refer to an event which hypothetically might have caused death if it were more severe.  **Other ‘important medical events’ may also be considered serious if they jeopardise the participant or require an intervention to prevent one of the above consequences. |

## Reporting procedures for all Adverse Events

AEs that are deemed directly related to study activities which are observed by the investigator or reported by the participant will be recorded in the participant’s medical records and an AE log from the time the participant is randomised. The following information will be recorded: description, date of onset and end date, severity, assessment of relatedness to study, and action taken. Additional follow-up information should be provided as necessary. AEs considered related to the study as judged by a medically qualified investigator or the sponsor will be followed until resolution, or the event is considered stable.  All related AEs that result in a participant’s withdrawal from the study or are present at the end of the study, should be followed up until a satisfactory resolution occurs.

It will be left to the investigator’s clinical judgement whether an AE is of sufficient severity to require the participant’s removal from treatment. A participant may also voluntarily withdraw from treatment due to what he or she perceives as an intolerable AE.  If either of these occurs, the participant must undergo an end of study assessment and be given appropriate care under medical supervision until symptoms cease or the condition becomes stable. The severity of events will be assessed using the following scale: 1 = mild, 2 = moderate, 3 = severe. AE’s will be recorded within the participant’s medical records and an AE log. Any safety concerns that arise because of this, will be reported to the sponsor as soon as possible.

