## Randomisation

Randomisation will occur after baseline assessments. Eligible participants who are living with MLTCs and frailty (and their carer if included) will be randomised in a 2:1 ratio to one of two arms:

- Intervention group: the PERSONAL-AGILITY intervention

OR

- Control group: usual care

The increased ratio of participants within the intervention group will give increased opportunity and exposure to the delivery of the intervention, which will be beneficial to refining and improving it for a future definitive trial.

Stratification will be based on one factor, frailty status, creating two strata (very mild and mild/ moderate and severe). Randomisation and treatment allocation will be performed using a third-party service using variable block sizes of 3 and 6.

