## Reporting Procedures for Serious Adverse Events

All SAEs (except from those outlined as expected) occurring from the time of randomisation until the final study visit must be reported to the Sponsor immediately and within 24-hours of becoming aware of the event. The SAE will be reported using appropriate forms and according to the Sponsor SOP for reporting serious adverse events. Additional information will be provided if requested to the Sponsor and main Research Ethics Committee (REC). The PI or a delegated physician (as agreed by the Sponsor) is responsible for the review and sign off of the SAE and the assessment of causality (i.e., whether an event is related to a study procedure or intervention).

The Sponsor will perform an initial check of the information and ensure that the SAE line listing is reviewed by the Director of Research & Innovation. All SAE information must be recorded on an SAE form and sent to the Sponsor. Additional information received for a case (follow-up or corrections to the original case) needs to be detailed on a new SAE form and sent to the Sponsor. Copies of all documentation and correspondence relating to SAEs will be stored in the trial master file (TMF).

For each **SAE** the following information will be collected:

- Full details in medical terms and case description
- Event duration (start and end dates, if applicable)
- Action taken
- Outcome
- Seriousness criteria
- Relationship to the study procedure or intervention

Any change of condition or other follow-up information should be emailed to the Sponsor immediately and within 24-hours of the information becoming available. Events will be followed up until the event has resolved or a final outcome has been reached.

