## Secondary trial outcome analysis

Outcomes at 12- and 24-weeks follow-up will be summarised by randomised group and overall using mean (SD) and median (IQR) for continuous variables and count (percentage) for categorical variables. The number of SAEs will be presented overall and by randomised group.  All exploratory analyses will be considered hypothesis generating rather than providing firm conclusions and no p values will be reported.

Outcome acceptability will be determined by quantifying the amount of missing data across the secondary outcomes. The proportion of missing data (number, %) will be reported for each outcome, but no imputation will be performed to account for this missing data. Reasons for missing data will be gathered where possible.

Quantitative acceptability data including:

- rates of uptake and engagement with each component of the PERSONAL-AGILITY intervention
- adherence to the intervention (e.g., frequency, intensity, time and type of activity)

will be reported descriptively using number and percentage.

PROMS relating to intervention acceptability (the 9-item shared decision-making questionnaire) will be examined descriptively, by reporting at 12- and 24-weeks follow-up using mean (SD) and median (IQR).

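### Adverse event recording starts only after the baseline tests, and non-serious events are logged only if judged study-related, against the protocol's own schedule and definition

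*Protocol*

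**What the plan says.** **Which AEs are logged, and from when (8.2).** "AEs that are deemed directly related to study activities which are observed by the investigator or reported by the participant will be recorded", and this runs "from the time the participant is randomised". For each logged event the items include "severity, assessment of relatedness to study, and action taken". A later sentence in 8.2 says that AEs go into the medical records and an AE log, with no condition on relatedness.

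**SAEs (8.4).** All SAEs, except those listed as expected, "occurring from the time of randomisation until the final study visit must be reported to the Sponsor". Causality is assessed after reporting and is not a condition for it. The exception in 8.3 covers outpatient and GP appointments, or treatments, for conditions already present at the start.

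**When randomisation happens (6.6).** "Randomisation will occur after baseline assessments". The footnote to Table 1 agrees.

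**Schedule (Table 1, section 6.1).** Adverse event reporting is marked for all participants at baseline, week 12 and week 24.

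**Definition (Table 4, section 8.1).** An AE is any untoward occurrence in temporal association with the study, irrespective of whether it is thought to be related.

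**Risks the protocol names.** In 7.9.1, for frailer participants, "objective tests of physical function such as the SPPB may make some people feel uncomfortable or unsteady". In 7.9.2, on the risks of becoming more active: "These include a slightly elevated risk of falls for people who have had a previous fall".

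**Safety summary (9.5).** "The number of SAEs will be presented overall and by randomised group".

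**The concern.** There are two separate problems.

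The first is the start of the recording window. The baseline battery includes the SPPB and the Berg Balance Scale, in people with a Clinical Frailty Scale score of 4 to 7. If recording begins at randomisation, a fall or injury during those tests lies outside the safety rules, although the protocol itself warns about unsteadiness on testing.

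The second is the use of relatedness as a condition for entering the log. Participants, intervention providers, study team and outcome assessors all know the allocation. Someone in the intervention arm who falls while being more active has a plausible link to study activity. A control, who receives assessments, generic information and usual care, rarely will. The same non-serious fall can then be logged in one arm and not in the other.

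A feasibility trial in a frail population should tell the definitive trial how often testing or intervention is followed by a fall. Events that were never written down cannot be tabulated by any later analysis plan.

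**Working it through.** The protocol states no AE rate, fall rate or safety figure, so there is nothing to reproduce. The main check is to set the text side by side.

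**Start of recording**

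1. Sections 8.2 and 8.4: AE and SAE capture begins at randomisation.
2. Section 6.6 and the Table 1 footnote: randomisation comes once baseline measures are complete. Section 6.5 lets those measures spread over as much as 14 days.
3. Table 1: adverse event reporting is due at baseline.

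Table 1 can be read in two ways. If its entry covers the whole baseline visit, it contradicts 8.2 and 8.4. If it means only from randomisation onwards (the randomisation row sits in the same column), there is no contradiction, but the baseline tests are then plainly uncovered. Either way the text needs repair.

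Extent: one of three assessment visits. Section 7.2 has carers do the same tests, so up to 50 + 50 = 100 people are affected.

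**Relatedness**

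1. The first sentence of 8.2 admits only related events.
2. Table 4 defines an AE without regard to relatedness.
3. Section 8.2 lists relatedness as an item to record, which is close to redundant if every logged event is already related.
4. The later logging sentence in 8.2 carries no such limit.

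These cannot all be followed at once.

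**Illustration of the effect on capture (assumed inputs)**

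Let *s* be the share of falls that are serious (captured whatever their cause) and *r* the share of non-serious falls judged study-related. The share of falls after randomisation that is recorded in an arm is

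c = s + (1 − s) × r.

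With the same true fall risk in both arms, the apparent risk ratio is c(intervention) / c(control). The fall rate cancels. Fifty people at 2:1 gives about 33 and 17, so the overall share recorded is (33 × c(intervention) + 17 × c(control)) / 50.

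| s | r, intervention | r, control | c, intervention | c, control | Apparent ratio | Overall share recorded |
|---|---|---|---|---|---|---|
| 5% | 10% | 0% | 14.5% | 5.0% | 2.90 | 11% |
| 5% | 50% | 10% | 52.5% | 14.5% | 3.62 | 40% |
| 10% | 30% | 5% | 37.0% | 14.5% | 2.55 | 29% |
| 20% | 10% | 0% | 28.0% | 20.0% | 1.40 | 25% |
| 20% | 50% | 10% | 60.0% | 28.0% | 2.14 | 49% |

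First row in full: 0.05 + 0.95 × 0.10 = 0.145 against 0.05, ratio 2.90; (33 × 0.145 + 17 × 0.05) / 50 = 0.11.

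Nine combinations were run: s of 5, 10 and 20%, each with the (intervention, control) pairs (10%, 0%), (30%, 5%) and (50%, 10%). The apparent ratio ran from 1.4 to 3.6 and the share recorded from 11% to 49%. The ratio is 1 when *r* is the same in both arms, so the distortion comes entirely from attributing falls to the study more often in one arm.

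**The case against.** Much can be said for the protocol.

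- **Serious falls are covered after randomisation.** A fall leading to hospital admission or significant disability is an SAE, is reported whatever its cause, and is counted by arm under 9.5. Non-serious falls judged related are logged. A reader might infer that falls are never captured or compared; 8.4 and 9.5 rule that out.
- **Test-related harm is not invisible.** The same tests are repeated at weeks 12 and 24 in both arms, so on the strictest reading it is recordable at two of three visits. Events before randomisation also cannot bias a comparison between arms. Both points stand, but they do not justify leaving the baseline tests uncovered.
- **There are other routes to harms.** Section 7.9.1 has PROMs reviewed at once, with new injury among the signs of concern, but that leads to referral and not to the AE log. Interviews ask about unintended harms, but 7.3.1 confines them to the intervention arm and excludes people withdrawn for illness or injury.
- **Tabulation belongs in the SAP.** This is right for percentages, participants with at least one event and person-time, and no point is made of their absence. It does not answer the capture rule.
- **2:1 allocation and SAE counts.** A reader might infer that raw counts would make the intervention look nearly twice as harmful at equal risk (33 / 17 = 1.94). The documents do not support this as a fault: 9.2 commits to a CONSORT diagram and baseline summaries by group, so the arm sizes will be on view.

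**Conclusion.** The point holds in limited form. As written, 8.2 and 8.4 leave harms from baseline testing outside AE and SAE recording while Table 1 points the other way. Section 8.2 also uses relatedness as an entry condition, against Table 4 and its own later text. Followed literally, non-serious falls judged unrelated go unrecorded in both arms, and the share of falls that reaches the log can differ by arm.

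The inconsistency of the text rests on no assumption. The unequal capture rests on staff attributing falls to the study more often in the intervention arm, which is plausible given open allocation and the little study activity in the control arm. Its size is not known: 1.4 to 3.6 is an illustration on assumed inputs. A reader might also infer from the illustration that most falls would be missed; no figure in the protocol supports or refutes that.

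This should be fixed before participants are assessed, because unrecorded events cannot be reliably recovered. It is not critical: neither the primary feasibility outcomes nor the progression criteria in Table 5 include a safety measure, so no planned decision is miscalculated.

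**What to change.** 1. Reconcile Table 1, Table 4, 8.2 and 8.4 on one start point: record AEs and SAEs from consent or from the first study procedure.
2. In 8.2, keep relatedness as a recorded field and remove it as a condition of entry, at least for falls and fall injuries.
3. At the existing week 12 and week 24 visits, ask every participant in both arms the same question about falls and fall injuries since the last visit, and log every positive answer.

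The cost is protocol wording, one short CRF item at visits already planned, and somewhat more AE entries to process. No extra visit is needed, and how the events are tabulated can be left to the SAP.

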## Schedule of procedures

Table 1. Schedule of procedures for the PERSONAL-AGILIY study.

|  | Screening | Consent | Baseline | Week 12 | Week 24 |
| --- | --- | --- | --- | --- | --- |
| Screening* | A |  |  |  |  |
| Consent |  | A |  |  |  |
| Demographic and Medical History# |  |  | A |  |  |
| Body Composition |  |  | A | A | A |
| Blood Pressure |  |  | A | A | A |
| Handgrip Strength |  |  | A | A | A |
| Short Physical Performance Battery (SPPB) |  |  | A | A | A |
| Berg Balance Scale |  |  | A | A | A |
| Physical Activity** |  |  | A | A | A |
| Sedentary Behaviour** |  |  | A | A | A |
| Sleep** |  |  | A | A | A |
| EuroQol-5 Dimensions |  |  | A | A | A |
| Short Form-36 |  |  | A | A | A |
| Late Life Function and Disability Instrument |  |  | A | A | A |
| Patient Outcome Scale |  |  | A | A | A |
| Goal Attainment Scale |  |  | A | A | A |
| Zarit Burden Interview |  |  | C | C | C |
| The 9-item Shared Decision-Making Questionnaire (intervention group only) |  |  |  | A | A |
| The 24-hour Physical Behaviours Burden Questionnaire (intervention group only) |  |  |  | A | A |
| Randomisation*** |  |  | A |  |  |
| Adverse Event Reporting |  |  | A | A | A |
| Interviews |  |  |  |  | A |

A = All participants; P = People with MLTCs and frailty only;C = Carers only.* Screening includes checks for confirmation of eligibility, as described in section 5. #Demographic and medical history includes: sex, date of birth, ethnicity, employment, education, marital status, socio-economic status, and a detailed past medical history including previous or current diseases and surgical interventions will be recorded by the study clinician on the CRF. **Physical activity, sedentary behaviour and sleep will be measured by an accelerometer. Measures include: Device measured steps, MVPA, sedentary behaviour, sleep quality and sleep duration.^***^Randomisation will occur on completion of baseline measures.

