### Accelerometer and inclinometer measured physical behaviours

At baseline, weeks 12 and 24, we will aim to assess physical activity, sedentary behaviour and sleep parameters objectively using accelerometery worn for approximately 9 full days (24-hours per day) to capture 3-4 days with >10 hours of valid wear time^96^. Two devices (one wrist-worn, GeneActiv (accelerometer), on the non-dominant side, and the other, activPAL (inclinometer) placed on the thigh) will be worn. The GeneActiv will capture triaxial acceleration data and data will be processed using an open-source R programme (GGIR) according to SOPs developed for the NIHR Leicester Biomedical Research Centre^97^. Postural allocation (sitting and standing) and walking will be quantified using an activPAL physical activity monitor (PAL Technologies, Glasgow, Scotland). The activPAL is a single-unit monitor based on a triaxial accelerometer that is worn midline on the anterior aspect of the thigh and attached directly onto the skin using medical dressing. The monitor produces a signal related to thigh inclination and has been shown to be a valid and reliable measurement tool for determining posture during activities of daily living in a healthy population. Participants will be given a daily log sheet to record their sleep times each day and any times that they may have removed the monitor, to facilitate future analyses.

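### Sections 8.2 and 8.4 start adverse event recording at randomisation, after the baseline function tests, and this conflicts with the baseline entry for adverse event reporting in Table 1

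*Protocol*

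**What the plan says.** Section 8.2 (Reporting procedures for all Adverse Events) covers "AEs that are deemed directly related to study activities which are observed by the investigator or reported by the participant" and enters them in the medical records and "an AE log from the time the participant is randomised". Section 8.4 (Reporting Procedures for Serious Adverse Events) sets the matching rule: events "occurring from the time of randomisation until the final study visit must be reported to the Sponsor immediately", apart from a short list of expected ones.

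The order of events is fixed elsewhere. Section 6.6 states: "Randomisation will occur after baseline assessments". The footnote to Table 1 in section 6.1 says: "Randomisation will occur on completion of baseline measures". Section 6.5 places the baseline measures after consent and before randomisation, and lets them spread over several visits within 14 days.

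The baseline measures include handgrip strength, the Short Physical Performance Battery (SPPB), the Berg Balance Scale and two body-worn devices, "worn for approximately 9 full days (24-hours per day" (section 7.2.3). Section 7.9.1 (Outcome testing), writing of frailer participants who may be more prone to falls, says that "objective tests of physical function such as the SPPB may make some people feel uncomfortable or unsteady".

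Table 1 also has a row for adverse event reporting. It is marked for all participants at baseline, week 12 and week 24.

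**The concern.** Once people have consented, they undergo study procedures that the protocol itself lists under risk. On the section 8 wording, the duty to log or report begins only when those procedures have been done once. A fall during the baseline SPPB, or a hospital admission during the baseline period, would fall outside both the adverse event log and serious adverse event reporting.

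This matters for two reasons. First, how well frail people tolerate the outcome tests is something a feasibility trial should tell the team planning the definitive trial, and events not recorded at the time are hard to recover later. Second, site staff have two instructions: Table 1 tells them to do adverse event reporting at baseline, and sections 8.2 and 8.4 tell them that the window is not yet open. Different staff may resolve this differently, and the count would then depend on who followed which section.

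**Working it through.** The protocol gives no event rate or expected event count, so there is no figure of its own to reproduce. The check sets the provisions side by side and counts testing occasions.

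**Timing**

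| Step | Source | Covered by 8.2 and 8.4? |
| --- | --- | --- |
| Consent | 6.2.8 | No |
| Baseline tests, up to 14 days | 6.5, Table 1 | No |
| Randomisation | 6.6, Table 1 footnote | Window opens |
| Week 12 tests | 7.1 | Yes |
| Week 24 tests | 7.1 | Yes |

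Table 1 marks adverse event reporting in the baseline column. Randomisation is marked in the same column, so the table alone does not show whether reporting starts before or after the tests. It can be read as covering baseline testing, which contradicts section 8, or as starting at the end of the baseline visit, which leaves the tests uncovered. Neither reading settles the matter.

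**Scope**

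Section 8.2 concerns events related to study activities, and section 8.4 asks whether an event is related to a study procedure or to the intervention. Baseline testing is a study procedure. A start at randomisation therefore leaves out part of what these sections set out to cover.

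**Share of planned testing occasions before the window opens**

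Inputs: 3 assessments per person (section 3); 50 people with multiple conditions and frailty, and up to 50 carers (Trial Summary).

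- Per person: 1/3 = 33%.
- People with multiple conditions and frailty: 50 × 1 = 50 of 50 × 3 = 150.
- With the maximum number of carers: 100 × 1 = 100 of 100 × 3 = 300.

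**With attrition**

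Share = 1/(1 + r12 + r24), where r12 and r24 are the proportions attending at weeks 12 and 24. Take r24 = 0.70, the green retention threshold in Table 5 (35 of 50). The protocol gives no figure for week 12, so r12 is assumed to lie between 0.70 and 1.00.

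- r12 = 1.00: 50/(50 + 50 + 35) = 50/135 = 37%.
- r12 = 0.70: 50/(50 + 35 + 35) = 50/120 = 42%.

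**After the change**

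With recording from consent, 3 of 3 occasions are covered: 150 of 150 instead of 100 of 150, or 300 of 300 instead of 200 of 300.

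**The case against.** The best reply is that Table 1 already schedules adverse event reporting at baseline for everyone, so baseline is not left out of the plan. That stands to this extent: a reader might infer from section 8 that baseline harms are never logged or reported, and the documents do not support so strong a statement. What remains is a conflict over the start of recording.

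It can also be said that participants are not unprotected at baseline. Section 7.9.1 has function tests done with another person present where possible, and participants may defer or stop. Section 7.1.1 counts attrition at each stage, including baseline, with reasons for withdrawal. This is fair, but it is not adverse event recording: section 7.8 lets people leave without giving a reason, and section 7.3.1 limits the participant interviews to those randomised to the intervention.

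Three further readings are tempting and should not be pressed.

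- **End of the window.** A reader might infer that week 24 device wear falls after the close of reporting. No section says when those devices are fitted, section 7.1 lets one time point span several visits, section 8.2 gives its log no closing date, and the only device risk named is discomfort.
- **Relatedness.** Section 8.1 defines an adverse event "whether or not considered related to the study", while section 8.2 logs only those deemed related. A broad definition with a narrower recording rule is not a contradiction, and a fall during a study test would ordinarily count as related to study activities. Section 8.4 has no relatedness filter.
- **Device wear at baseline.** The Table 1 footnote suggests that wear ends before allocation, but no section says so expressly. The point rests on the function tests alone.

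**Conclusion.** The point holds as an internal conflict with a practical consequence. Sections 8.2 and 8.4 start recording after the baseline tests, while Table 1 places adverse event reporting at the baseline visit. If staff follow section 8, events during 1 of 3 planned testing occasions need not be logged or reported. With the attrition assumed above, baseline makes up 37% to 42% of the occasions actually held.

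These figures measure testing occasions only. A reader might take them as the share of harms missed. That would need equal risk at every occasion and no harms outside testing, and the protocol supports neither: it gives no event rate, and harms arising during the intervention period fall inside the window.

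This should be corrected, but it does not threaten the trial's main conclusions. No progression criterion in Table 5 uses adverse event counts. The summary of serious adverse events by randomised group in section 9.5 is also unaffected, because events before randomisation belong to no arm.

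**What to change.** In sections 8.2 and 8.4, start adverse event logging and serious adverse event reporting at consent or, if preferred, at the first baseline procedure. Use the same start point in both sections. Add a note to the adverse event row of Table 1 stating that start point, so that it is clear that reporting at baseline begins before the tests and not after randomisation.

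In section 9.5, report pre-randomisation events on a separate line. The summary by arm, and the overall count among those randomised, then stay as planned.

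The cost is small: a wording change in two sections, a table note, one extra line in the safety summary, and a few more log entries, including some for people who consent but are never randomised.
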